## 6.2 Subjects

### 6.2.1 Recruitment

The medical device will be launched and promoted by the company LongLife Active AB as a real-world project. The ambition is to reach individuals in need of lifestyle change, with a special emphasis on hard-to-reach groups. Health care services, pharmacies, employers, benefit platforms (e.g. Benify and Epassi) and social media will be targeted. Employers may apply for the health promoting subsidy, Friskvårdsbidrag, when employees sign up for LongLife Active. Health care patients prescribed physical activity (Fysisk aktivitet på recept, FaR) from their care provider is allowed a reduced fee on the membership of LongLife Active®.

Individuals who sign up for the service from September 2023, or as soon as ethical approval is obtained, will be informed about the research study and invited to consent for data extraction. Controls will be recruited through social media at the same time frame.

#### *Inclusion criteria (intervention arms):*

- adults  $\geq 18$  years who sign up for the service LongLife Active using BankID for identification.
- consenting to the research study.

#### *Inclusion criteria (controls):*

- adults  $\geq 18$  years.

#### *Exclusion criteria (intervention arms):*

- individuals who are discharged from the app due to refracting the terms of the service
- subjects scoring  $>70$  on well-being will be excluded from the primary analyses (36)
- subjects who appear as friends, colleagues or family with anyone in the research or owner group.

#### *Exclusion criteria (controls):*

- age  $\leq 17$  years
- is currently using a digital product or any other kind of support for behavior change (e.g. Livsstilsverket, Health Integrator, Weight Watchers).
- is found to be a user of LongLife Active.
- subjects who appear as friends, colleagues or family with anyone in the research or owner group
- subjects scoring  $>70$  on well-being will be excluded from the primary analyses (36).

*Sample size:* The estimation is to reach 5000 consenting individuals in total for the intervention arms and 200 controls.

Total expected duration for each subject's participation: (intervention arms: 24 months, (controls)

*Drop-outs and discontinued use of the digital service:* Subjects who notify they would like to withdraw from the research study are disconnected to the data base. Subjects who discontinue using the digital service will be invited to continue the research participation and to answer the questionnaires online.

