## 2. Identification and description of the investigational device

### 2.1 Identification of the device

LongLife Active AB, 559267-4492 is a Swedish Life Science company based in Täby, Sweden. LongLife Active is the manufacturer of the digital health service LongLife Active® that is a mobile phone application (app) available to download at Google Play and App Store. The development of the investigational device runs in-house at a proprietary Swedish platform in collaboration with an interprofessional scientific advisory board. The scientific advisory board includes independent researchers in the fields of physical activity, nutrition, nursing, psychology, and computer science. Agreements on non-funded collaborations are signed between LongLife Active AB and each researcher. Supplement 2 lists the involved researchers.

LongLife Active® is a digital health service (mobile phone application) classified as a medical software device class I, following Regulation (EU) 2017/745 of the European Parliament and of the Council of 5 April 2017 on medical devices (1). LongLife Active® is managed and regulated following the Swedish standards Medical devices – Quality management systems – requirements for regulatory purposes (ISO 13485:2016), and Health software – Part 2: Health and wellness apps – Quality and reliability (ISO/TS 82304-2:2021).

The digital service is intended for adults (≥18 years) in need of behavioral support to adopt healthy habits and establish a healthy lifestyle. The digital service is independent of any other device. Hence, no external accessories are needed to enable the intended performance and purpose of the device.

The user can connect the digital service with digital activity trackers or an external mobile phone application for automatic registration of the user's physical activity level. All accessories accepted to be synced with the digital service have been regarded within the reported justification of classification and risk class of the medical device. No medical accessories are planned to be connected with the digital service.

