### 5. Objectives and hypothesis of the clinical investigation

#### 5.1 Main objective

I) The primary objective of this project is to evaluate the effectiveness of an individually tailored digital service aimed to support healthy habits among the adult population on well-being compared to a control sample of the general population.

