## 6. Design of the clinical investigation

### 6.1 Investigational device/Description of exposure

The medical device to be investigated is the mobile phone application (app) LongLife Active®. The app includes three core topics: 1) Healthy diet, 2) Physical activity, and 3) Mental balance. Supplement 4 shows the included intervention components and behavior change techniques. The service includes functions such as tracking and self-monitoring behavior and health outcomes, goal setting, action planning, a database with food recipes, a database with exercises, a database with relaxation exercises, skills training articles and webinars, live events, adjustable push notifications and gamification (rewards). If the user prefers there are options to pay extra for further social support: a version including a community (chat groups and group coaching sessions, live events and physical meetup events), and a version including the community plus the possibility to have a private health coach. The app is assisted by artificial intelligence to direct the support to the individual timely and based on the needs, motivation, preferences, experiences, opportunities, and capabilities of each user. The user decides which functions to use.

The literature review undertaken during the formative phase showed participants wished for interface design and reminders to be customizable, and that the service should be integrated with other services (such as shopping lists). These are examples of aspects that have been regarded to keep engagement over time. With a straightforward design, illustrations, and short video instructions the service is customized for people with low skills in the Swedish language or with low digital and/or health literacy.

No other medical devices or medications are to be used.

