## 11. Device accountability

Access to the investigated medical device will be controlled using electronic identification (BankID). Subjects in the control group will be excluded if they answer they are using some digital support for behavior change. In addition, a comparison of names and email addresses it will be made to check that the control subjects are not using the investigated medical device.

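### Other behaviour-change support is an exclusion for controls but not for subscribers, so the primary well-being contrast cannot be attributed to the app alone

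*Protocol*

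**What the plan says.** **Controls.** Protocol Section 6.2.1 excludes a control who "is currently using a digital product or any other kind of support for behavior change", and the synopsis (Section 1.6) repeats the rule. Section 11 describes how it is applied: "Subjects in the control group will be excluded if they answer they are using some digital support for behavior change". Section 7.4 also expects some controls to be lost in this way, and mentions digital products only.

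**Intervention arms.** Section 6.2.1 admits adults "who sign up for the service LongLife Active using BankID for identification" and who consent. There are three exclusions: "individuals who are discharged from the app due to refracting the terms of the service", a WHO-5 score above 70 (for the primary analyses), and personal ties to the research or owner group. None concerns other support.

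**Objective and analysis.** Section 5.1 evaluates the service "compared to a control sample of the general population". Section 7.3 analyses change in well-being with a mixed model for repeated measures and names intervention level and time as its terms. Table 1 has no row for concurrent support.

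**The concern.** The groups are not randomised, so eligibility is one of the few tools the plan has for making them comparable. Here the eligibility rule makes them less alike. A member of a commercial weight-loss programme is barred as a control but accepted as a subscriber. Any effect of such a programme can therefore enter the intervention mean and can never enter the control mean.

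What is at stake is the interpretation of the primary result. Section 5.1 asks about the effect of the service. The planned contrast answers a different question: subscribing, alongside whatever else the person is doing, against doing nothing supported. If other support is not recorded at sign-up, no later analysis can separate the two.

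**Working it through.** No stated figure of the plan is in dispute, so the check is first a comparison of texts.

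| Item | Controls | Intervention arms |
|---|---|---|
| Other digital product | Excluded (1.6, 6.2.1, 11) | No rule |
| Other non-digital support | Excluded (1.6, 6.2.1); not mentioned in 11 | No rule |
| WHO-5 above 70 | Out of the primary analyses | Out of the primary analyses |
| Ties to research or owner group | Excluded | Excluded |

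The last two rows show that the plan does apply common rules where it wants them. The first two rows are one-sided. Two further points follow from the texts:

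- *Scope.* Section 6.2.1 covers every kind of support, whereas Section 11 covers digital support only. A control in a non-digital programme is excluded under one and not mentioned in the other.
- *Timing.* Section 6.2.1 is worded in the present tense and reads as status at entry. Section 11 gives no time point.

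**Illustration of size (assumed inputs).** Let *q* be the share of analysed subscribers with other support, and *e* the extra WHO-5 gain that this support produces after month 0, independently of the app. With no control using such support, bias = *q* × *e*. The documents give neither input. The assumed ranges are *q* = 10-50% and *e* = 5-12 points.

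| | *q* = 10% | *q* = 20% | *q* = 50% |
|---|---|---|---|
| *e* = 5 | 0.5 | 1.0 | 2.5 |
| *e* = 10 | 1.0 | 2.0 | 5.0 |
| *e* = 12 | 1.2 | 2.4 | 6.0 |

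Against the 12-point target in Section 7.4, this runs from 0.5/12 = 4% to 6.0/12 = 50%.

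**Effect on a null result.** Inputs from Section 7.4: SD 19.9, two-sided 5% test, 75% drop-out, 20% removed for a score above 70. The subscriber arms are pooled for simplicity.

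- Analysed subscribers: 5000 × 0.80 × 0.25 = 1000.
- Analysed controls: 200 × 0.80 × 0.25 = 40, or 200 × 0.80 = 160 if none drop out.
- Standard error: 19.9 × √(1/40 + 1/1000) = 3.21, or 19.9 × √(1/160 + 1/1000) = 1.69.
- With an app of no effect and a bias of 2 points, the false-positive rate is 9.6% (40 controls) or 21.9% (160 controls), instead of 5%.

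**Cost in precision of a common rule.** Even if half of the analysed subscribers left the primary set, the standard error would be 19.9 × √(1/40 + 1/500) = 3.27 instead of 3.21, or 19.9 × √(1/160 + 1/500) = 1.81 instead of 1.69. Precision is limited by the controls.

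**The case against.** Several arguments on the other side are sound and limit the point.

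- **Use of other support by subscribers is not documented.** A reader might infer from "Health care patients prescribed physical activity (Fysisk aktivitet på recept, FaR) from their care provider is allowed a reduced fee" that recruitment targets people already in a rival programme. The text does not say that. It describes a discount, and the app may be how the patient follows the prescription. Likewise, "The user can connect the digital service with digital activity trackers or an external mobile phone application" describes automatic registration of activity, not a competing intervention.
- **The direction is conditional.** Section 7.3 analyses change with month 0 in the model. Support already in place at sign-up is at least partly reflected in the baseline score. If those users have already improved, the bias could run against the device. Hypothesis 1 in Section 5.3 is worded as a difference in 6-month means, so the concern does not disappear.
- **Removal of controls during follow-up is not planned.** A reader might infer from Section 11 that a control who takes up support later is dropped, against the intention-to-treat approach in Section 7.1. No text provides for re-screening. This is a risk from loose wording, not a contradiction.
- **The description of the comparator mainly names the recruitment source.** A no-support comparator is a legitimate choice, but it then calls for the same restriction among subscribers.
- **The case report form (Supplement 6) is not shown and may record other support.** Table 1 also omits the question that Section 11 shows controls are asked. Covariates may be settled in an analysis plan that is not at hand. Either would help adjustment, but the eligibility rule would remain unequal.

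The sentence "No other medical devices or medications are to be used" does not answer the concern. It stands in the description of exposure in Section 6.1, is not an eligibility criterion, and does not reach support that is neither a device nor a medication.

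**Conclusion.** The unequal rule is explicit in the synopsis and Section 6.2.1, and nothing in the protocol compensates for it. The primary contrast compares the app, with or without other support, with no support, so it cannot be credited to the app alone. The bias favours the device only if some subscribers use other support and that support adds to WHO-5 after month 0. The protocol supplies neither quantity, so the size is unknown. The 0.5 to 6.0 points above, and the false-positive rates, show only what the assumed inputs imply.

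A reader might go further and infer that the device is being credited with the effects of other programmes. The documents do not show this; they only leave it possible. Self-selection of subscribers against volunteer controls is a separate source of confounding and would remain under any common rule. This is an avoidable imbalance made by the plan's own wording, and a cheap improvement.

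**What to change.** 1. Ask subscribers at month 0 the same question on other behaviour-change support that controls answer.
2. Apply one rule in the primary well-being analysis: restrict both groups to subjects without other support at month 0. Report an analysis of all subscribers against the controls as a sensitivity analysis.
3. Describe the comparator in Sections 1.6 and 5.1 as people from the general population who are not using behaviour-change support.
4. Align Section 11 with Section 6.2.1 so that both cover the same kinds of support. State that status is fixed at month 0, so that controls who start support later stay in the analysis.

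The cost is one extra question at sign-up, a few sentences in the protocol, and the loss of some subscribers from the primary set. With 5000 planned, that loss has little effect on precision. The change does not remove confounding from people choosing and paying for the app.

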## 6.3 Procedures for data collection

### 6.3.1 Procedures

This investigation will take place outside the clinical practice. Data will be collected by self-reported instruments (questionnaires) and analytics from the digital service. An exception from self-reported measures is that an activity monitor will be used to measure physical activity and sedentary behavior besides self-reported instruments. Supplement 6 Case Report Form shows the included questionnaires with details on specific questions and response alternatives. Reminders to answer the questionnaires will be pushed out weekly for 4 weeks until the subject has answered (max 4 reminders). The activity monitor will be posted to the subjects together with instructions and a log to write the time when the monitor was put on and off during the day. It should be placed on the thigh and worn for 7 consecutive days. The subject will be asked to fill out the diary for wake-up time and bedtime, and for major physical activities performed during the day.

Answering questionnaires and wearing the activity monitor is voluntarily, and if the subject does not answer it will not affect his/her use of the app.

There is a risk of selection bias affecting the results. We believe highly motivated subjects (responders) possibly answer the questionnaires to a larger extent than subjects facing more challenges.

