The response rate of the initial questionnaire was 64%. On a question about the initial screening questions, 59% agreed that these questions were relevant to their lifestyle. Concerning assistance with goal setting, 31% found that the LongLife Active service was good/very good in helping them to concrete their goals and 22% experienced the service was bad/very bad in concreting their goals. The goal setting function has been improved fundamentally since. In all, 69% felt good/very good and 40% very good about leaving personal or sensitive information in the service, and only 3% (1 participant) felt bad about this.

The response rate of the questionnaire covering the perceived usability of the service collected by the System Usability Scale (SUS) at week 3 was 30%. The overall SUS score was 50.0, which is an OK rating, one that is slightly below the average (32). Acceptability was assessed by the Mobile Application Rating Scale (MARS) at the same time point. The score is out of 5 and indicate overall app quality. The overall MARS score was 3.27, which is considered to be acceptable (3). The mean scores for all the sections were: engagement = 2.97, functionality = 2.83, aesthetics = 3.29 and information quality = 4. No adverse events or dissatisfaction were reported.

The seemingly low response rates to the questionnaires and reduced engagement over time were expected. The findings from the pilot study, especially the individual interviews, have powerfully guided further development and optimization of the digital service and the design of the clinical evaluation.

Another pilot study including 20 individuals with type 2 diabetes who tested the device for 1 months was completed in April 2023. The participants gave constructive feedback on the usability and value of the device. Twelve of the participants were interviewed and their comments have been very useful for adapting and optimizing the device, especially the action plan and goal setting functions. A manuscript describing the findings is in progress.

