## 7. Statistical design and analysis

### 7.1 Analysis population

For the endpoint well-being an intention-to-treat approach will be applied. By using mixed model for repeated measures all subjects with two or more measurements will be included in the analysis and manual imputation is not needed. For the intermediate outcomes dietary habits, physical activity, and mental health only subjects who have set up change goals within the area will be analysed.

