### 7.4 Sample size calculation

The endpoint well-being will be assessed using the WHO-5 Well-being Index (34). In our pilot study the mean score at baseline was 55. The instrument has to our knowledge not been applied on a general Swedish population. In Danish general population surveys, the mean WHO-5 score was 60-70 ( $sd=19.0-19.9$ ) (36, 47, 48). A change of 10-20 points in WHO-5 has been proposed as a clinically relevant change (36, 49). In up-scaled interventions 60% lower effects are expected (50). We therefore aim at a difference of 12 points in the score between intervention groups and control group as well as between baseline and 6 months. A fluctuation in well-being is considered normal (36), subjects with well-being score  $>70$  are not expected to improve and will be excluded from the analysis. In the pilot study 21% of participants reached 70 points at baseline.

Desirable sample size was calculated to detect an effect of 12 points (36, 51) based on the assumption of two-tailed testing, an alpha error  $\alpha=0.05$  and power  $1-\beta=0.90$  and  $sd=19.9$  (48). To detect a medium standardised effect size of 0.5 (Cohen's d) for the primary outcome well-being at 6 months a sample size of at least 25 subjects per group is recommended. Expected drop-out rate due to withdrawal and lost to follow-up at six months is 75 %. Based on the expected drop-out rates and on excluding 20% from the analysis due to baseline score  $>70$ , we need to recruit at least 500 subjects to assure 25 subjects in each intervention arm. In the control group we assume subjects to be excluded based on using a digital product for behavior change and strive to include 200 subjects.

The secondary outcomes are exploratory due to the person-centred design of the service. The subjects will set individual goals and possibly change goals during the intervention. Likewise, habits and behavior change are largely changeable due to circumstances. The current research is not immense enough to guide a decision for minimal expected effects when individual goals are set (e.g., reducing weekly servings of red meat). A larger sample size than what is required for the primary

endpoint well-being is desired. Similarly, the secondary analyses of mediating factors and responsiveness require a large sample size. We therefore aim to include 5000 subjects.

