## 13. Informed consent process

Individuals who sign up for the digital service LongLife Active from October 2023 (or as soon as ethical approval is obtained) will be informed about the research study (informed consent in supplement 5a) and invited to consent for data extraction in the app. Controls will be recruited through social media and through large companies and will be sent the detailed information by email (supplement 5b). Control subjects consent in the survey tool before starting to answer the questionnaire.

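### For app users, unlike controls, the baseline WHO-5 behind the >70 exclusion can be given after app use starts or be absent, so the same cut-off screens the groups differently

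*Protocol*

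**What the plan says.** **The cut-off.** In section 6.2.1 the exclusion criteria for both groups state that subjects scoring above 70 "on well-being will be excluded from the primary analyses". The criterion names no time point. Section 7.4 supplies it, since the sample size allows for "excluding 20% from the analysis due to baseline score" above 70.

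**Users.** Section 6.4 has questionnaires and reminders pushed through the app. Section 6.3.1 states: "Reminders to answer the questionnaires will be pushed out weekly for 4 weeks until the subject has answered (max 4 reminders". It also says: "Answering questionnaires and wearing the activity monitor is voluntarily", and adds that not answering has no effect on use of the app. Under section 15 a user's follow-up clock starts at the first registered activity.

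**Controls.** Section 13 states: "Control subjects consent in the survey tool before starting to answer the questionnaire". Under section 15 a control's clock starts when the first questionnaire is submitted, and follow-up ends 7 months later.

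**Analysis.** Section 7.1 says that "all subjects with two or more measurements will be included in the analysis". Section 7.3 puts months 0, 6, 12, 18 and 24 in the model. The primary endpoint is well-being at 6 months.

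**The concern.** The cut-off is there because people above 70 are not expected to improve (section 7.4). For the comparison to be fair, it must act on the same quantity in both groups, namely well-being before exposure. As written it does so for controls but not necessarily for users. Two things can go wrong, and only on the users' side.

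1. **Late score.** A user who answers month 0 after starting to use the app gives a score that may already contain some effect. If it has risen above 70, an early improver is removed. If it has not, part of the gain is counted as baseline. Both reduce the apparent benefit.
2. **No score.** A user who skips month 0 but answers months 6 and 12 meets the section 7.1 rule without ever being screened. Some of these users will have started above 70, which raises the users' 6-month mean whether or not the app works.

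Both bear on the single primary contrast. A score from before app use that was never collected cannot be recovered by any later analysis rule.

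**Working it through.** **Step 1: can it happen to users?** Answering is voluntary and app use continues without it (6.3.1). Questionnaires arrive through the app (6.4). The user clock starts at the first activity, not at the first answer (15). Section 2.2 requires consent before use and section 6.3.2 collects demographics at sign-up, but no section ties the WHO-5 to either moment. So yes, a late or absent month-0 score is possible.

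**Step 2: can it happen to controls?** Their entry is the first questionnaire (13, 15), so the first score is the entry score. Within the model times they have only months 0 and 6, because they leave at 7 months. A control with two such measurements therefore has the screening score. A slow control has had no exposure to the app in the meantime.

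**Step 3: check the cut-off against the plan's own figure.** Inputs from section 7.4: pilot baseline mean 55; SD 19.9 (a Danish population figure, assumed to hold for users). Normality is assumed.
- z = (70 − 55)/19.9 = 0.754, so P(>70) = 22.5%. This is close to the plan's 20%, and to the 21% who reached 70 in the pilot.
- Mean of those at or below 70: 55 − 19.9 × φ(0.754)/Φ(0.754) = 55 − 7.7 = 47.3.

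Screening thus lowers the expected baseline mean by 7.7 points.

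**Step 4: no score.** Let u be the share of analysed users without a screening score and r the correlation between baseline and month 6. If unscreened users are otherwise like all users and the SD is unchanged, the users' 6-month mean is higher than under full screening by u × r × 7.7, with no treatment effect. The documents give neither u nor r, so both are assumed.

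| u | r = 0.4 | r = 0.8 |
|---|---|---|
| 5% | 0.05 × 0.4 × 7.7 = 0.2 | 0.05 × 0.8 × 7.7 = 0.3 |
| 10% | 0.3 | 0.6 |
| 36% (extreme) | 1.1 | 0.36 × 0.8 × 7.7 = 2.2 |

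**Step 5: late score.** Assume a user who answers late has already gained 3 or 6 points.
- Among late answerers, P(>70) becomes 27.3% (mean 58) or 32.6% (mean 61). The mean recorded baseline of those kept becomes 48.9 or 50.4 instead of 47.3.
- If 20% of users answer late (assumed), the overall excluded share is 0.8 × 22.5 + 0.2 × 27.3 = 23.5%, or 0.8 × 22.5 + 0.2 × 32.6 = 24.5%, against 22.5%.

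**Step 6: direction.** Step 4 raises the users' result and step 5 lowers it. The net direction is not fixed.

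**The case against.** The strongest reply is that baseline windows and missing baselines are ordinary matters for a statistical analysis plan. On this view the protocol is consistent in what it does fix: WHO-5 at month 0 in Table 1, exclusion on the baseline score in section 7.4, and questionnaire timing controlled by the investigators in section 6.4. The reminder sentence covers all questionnaires and does not say that a month-0 answer four weeks on counts as baseline. This stands in part, because a window could be set elsewhere. But the rule of two or more measurements, the different clock starts and the voluntary answer are fixed here, and a plan written later cannot create a score that was not collected.

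Four stronger readings are tempting, and the documents do not support them.

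- **That 36% of users would be unscreened.** Section 3.3 says "The response rate of the initial questionnaire was 64" per cent, but the items reported from it concern the relevance of the screening questions, help with goals and comfort with sharing data. It is not shown to have contained the WHO-5. Nor is non-response among those enrolled the share among those analysed: an unscreened user must ignore month 0 and its reminders, then answer at least two later time points, where section 7.4 expects 75% loss by month 6. Hence 36% serves only as an extreme upper assumption.
- **That exclusions would rise to 27–33%.** That would require every user to answer late.
- **That the damage could not be traced afterwards.** Analytics are saved continuously, so late or absent baselines should be identifiable. What is lost is the value before app use.
- **That four weeks is the limit.** It is inferred from the reminder schedule. No section closes the window, and none separates a late month-0 answer from the month-1 WHO-5 in Table 1.

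**Conclusion.** The point holds as a difference between the groups in how the cut-off operates. Followed as written, sections 6.3.1 and 7.1 let users, but not controls, enter the primary analysis unscreened or screened on a score given after app use began.

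Its size is unknown. With a normal baseline (mean 55, SD 19.9), 5–36% of analysed users unscreened and a correlation of 0.4 to 0.8, the users' 6-month mean is raised by about 0.2 to 2.2 points with no effect. With 20% answering late after a gain of 3 to 6 points, the excluded share rises by 1 to 2 percentage points. Against a 12-point target both are modest, and they oppose each other.

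A reader might infer that the primary comparison is invalid for this reason, or that it is biased in favour of the app. The documents support neither: they do not show how often either failure occurs, and the sign of the net effect is open. It is a flaw worth correcting before recruitment, since it concerns data capture and the correction is cheap.

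**What to change.** 1. **Data capture.** Place the five WHO-5 items directly after the consent screen, before app functions open, and keep them voluntary.
2. **Sections 6.2.1 and 7.1.** Define the primary well-being analysis set in both groups as subjects with a month-0 WHO-5 of 70 or less, completed before the first registered app activity (users) or at entry (controls). A reminder-prompted answer still counts if it precedes first app activity. Barring all such answers would drop valid untreated scores and worsen the responder selection that section 6.3.1 already acknowledges.
3. **Sensitivity.** Report users with a late or absent baseline in a separate sensitivity analysis.

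**Cost.** The change needs protocol wording and one screen in the sign-up flow. Users who skip the baseline leave the primary set. In numbers this is bearable: on the plan's own rates, 5000 × 0.25 × 0.80 = 1000 users would be analysable at 6 months, and even the extreme 36% loss would leave 640. The real downside is that the set becomes narrower than the one in section 7.1 and may favour motivated responders. The number and characteristics of those left out should therefore be reported.
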